##### Data Collection

The primary outcome of diet quality was planned to be measured using a 32-item food frequency questionnaire which was developed with and for remote Aboriginal populations [40]. A Dietary Guideline Index score (score 0–100) [41], validated in a similar population [42], measuring the degree of adherence of the diet to the Australian Dietary Guidelines was planned to be calculated. Optional feedback to participants about their diet based on their score at follow up data collection was included in the design. The affordability of a healthy diet was planned to be measured at baseline and follow up [36].

A modified version of the United States Department of Agriculture 18-item Household Food Security Scale Module [43], which has been validated and used in research in Australia [44,45], was planned to be used to measure the prevalence of food insecurity. Haemoglobin data routinely collected at health clinics for two months prior to baseline up to strategy end were planned to be used to determine anaemia incidence and prevalence and will be compared between strategy and control communities at baseline and follow-up.

Contextual and supporting data includes demographic and household data for all participants, diet cost [36], minimum meal frequency data [46], an iron score and discount card purchasing data. All data collection tools were planned to be tested initially with ACCHO staff, and where possible, with local community members prior to use (CREATE Tool item 8).

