##### Heathy Food Price Discount Strategy

The co-design team determined that the best approach to explore the value of a healthy food price discount strategy to support food security in remote communities was a controlled before-and-after design. The design included eligible participants having access to a discount card that unlocks price discounts on healthy food purchases in the community store. The primary outcome is the difference in the change from baseline in diet quality between participants in strategy and control communities. We also planned to assess how the discounted prices impacted affordability. Secondary outcomes include food security and anaemia.

In line with Apunipima’s targeted call, all Aboriginal and/or Torres Strait Islander pregnant and breastfeeding women, and parents/primary carers of children aged six months to five years who identify as a resident and plan to reside in the community for the trial period were eligible. Timelines for recruitment were to be directed by Community Advisory Groups to best avoid times of community business, therefore respecting local community protocols (CREATE Tool item 5) and upholding the right for communities themselves to have control over data collection (CREATE Tool item 8). It was planned that one discount card identity be allocated per family, with up to three cards linked to the identity as requested by participants to meet their family needs. The design included three capped fortnightly levels of discount depending on the number of eligible household members: $80, $100, or $120 each fortnight for one, two, or three or more eligible people, respectively. It was estimated that $120 would promote an affordable diet in line with the accepted benchmark of food spend being 30% of household income for a family of four [36].

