We planned for the trial to be conducted in two strategy and two control communities in each region, totalling eight communities. Inclusion criteria included: (i) previous or expressed commitment from council, Health Boards, Health Action Teams, or other local governing bodies to support food and nutrition projects, (ii) existence of strong community groups, and (iii) for strategy communities, that the store operates a point-of-sale system to support the delivery of the discount strategy. We anticipated to have 240 participants in each of the intervention and control groups, 480 in total after non-consent and drop-out. This sample size enables 80% power to detect an improvement of four (SD = 12) points in diet quality between intervention and control communities, assuming high uptake of the strategy [37]. During our co-design meetings and based on our collective experience, three months was considered the minimum time required for participants to make changes to their purchasing [27]; therefore, the discount period was determined to be three to six months in each strategy community. It was planned that Community Advisory Groups participate in selecting foods targeted for discounting in their community store based on the five food groups and healthy fat group of the Australian Dietary Guidelines [38], and therefore have control over this critical aspect of strategy implementation (CREATE Tool item 8). The design included a discount of 30% applied to all approved healthy foods and drinks in each community, as this approximates the price gap between remote stores and supermarkets in Queensland [23,39].

The implementation of the healthy food discount strategy was planned to be monitored through fortnightly review of store data of discount card purchases and monthly visits to communities throughout the strategy period by the ACCHO project managers. A survey assessing participant satisfaction with the discount card and strategy was planned to be conducted with participants in strategy communities at follow-up to gain insight into the success of the strategy from the participant perspective, and any areas where improvement could be made. This is key for informing the sustainability of any potential future discount programs introduced through translation of this work into policy (CREATE Tool item 11).

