##### Data Analysis

The difference in Dietary Guideline Index scores and food security status between strategy and control communities will be reported. Dietary intake and quality, food security status, anaemia incidence and prevalence, and discount card use will also be described. Diet cost and affordability data will be analysed using existing purpose-built data spreadsheets [36].

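### Clinic haemoglobin is put to use only as anaemia yes/no, with no comparison of haemoglobin level named; adding one would be a cheap gain on a secondary outcome

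*Protocol article*

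**What the plan says.** The price discount strategy section under 3.5.1 names the outcome by condition, not by measurement: "Secondary outcomes include food security and anaemia". The Data Collection section gives the source as "Haemoglobin data routinely collected at health clinics for two months prior to baseline up to strategy end", and says that these data "were planned to be used to determine anaemia incidence and prevalence and will be compared between strategy and control communities at baseline and follow-up". The Data Analysis section returns to the outcome in one line: "Dietary intake and quality, food security status, anaemia incidence and prevalence, and discount card use will also be described".

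The article states no anaemia cut-off, expected prevalence, haemoglobin SD, expected shift or power for this outcome. Eligibility covers "pregnant and breastfeeding women, and parents/primary carers of children aged six months to five years", so more than one reference range may be involved. The primary outcome is treated differently: diet quality stays on its 0–100 scale and is compared as change from baseline.

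**The concern.** Haemoglobin arrives as a number for each person. Once it is classed as anaemic or not, a rise that stops short of the cut-off counts as no change, and so does a rise in someone who was already above it. Incidence has a further limit: people anaemic at baseline cannot become new cases, so their recovery does not enter it.

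Anaemia is the only named primary or secondary outcome that rests on a biological measurement; diet quality and food security both come from questionnaires. The discount lasts three to six months. If it moves haemoglobin modestly, a yes/no comparison may miss the movement, and a null anaemia result could be read as no biological effect.

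**Working it through.** **The plan's own figure.** There is none for anaemia. The only calculation concerns diet quality: "We anticipated to have 240 participants in each of the intervention and control groups, 480 in total after non-consent and drop-out", for "80% power to detect an improvement of four (SD = 12) points in diet quality between intervention and control communities". With two-sided 5%, n = 2 × [12 × (1.960 + 0.842) / 4]², which gives 142 per group; 240 is about 1.7 times that. It does not bear on this point, except that 240 is the largest per-group number the article offers.

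**Assumptions, none from the article.** Haemoglobin roughly normal; the same shift for everyone; independent observations; two-sided 5%; anaemia prevalence p from 5% to 50%.

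**Step 1: efficiency of the cut.** For a small shift, the information kept by the yes/no form is φ(z_p)² / [p(1 − p)], where z_p is the normal quantile of p and φ the normal density.

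| Anaemia p | φ(z_p)² | p(1 − p) | Kept | Lost |
|---|---|---|---|---|
| 5% | 0.0106 | 0.0475 | 0.224 | 78% |
| 10% | 0.0308 | 0.0900 | 0.342 | 66% |
| 20% | 0.0784 | 0.1600 | 0.490 | 51% |
| 30% | 0.1209 | 0.2100 | 0.576 | 42% |
| 40% | 0.1493 | 0.2400 | 0.622 | 38% |
| 50% | 0.1592 | 0.2500 | 0.637 | 36% |

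**Step 2: check at a finite shift.** For a 0.2 SD shift and 80% power, the continuous comparison needs 393 per group. The yes/no comparison needs 1,284 at 10% anaemia, 714 at 30% and 620 at 50%. The losses, 1 − 393/n, are 69%, 45% and 37%, in line with Step 1.

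**Step 3: what this does to power, for illustration.**

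- 0.2 SD shift, 240 per group: the continuous comparison has Φ(0.2/√(2/240) − 1.96) = Φ(0.23) = 59%. The yes/no comparison has 23%, 32%, 37% and 40% at 10%, 20%, 30% and 40% anaemia.
- 0.25 SD shift, 30% anaemia (falling to 21.9%): 78% against 53% with 240 per group, and 42% against 26% with 100 per group.
- Baseline adjustment with an assumed correlation of 0.5 multiplies the variance by 1 − 0.25 = 0.75 and raises the 78% to 89%, but only if all 240 per group have paired values.

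**Step 4: effect of clustering.** The design has "two strategy and two control communities in each region, totalling eight communities", so about 480/8 = 60 participants each. Clustering lowers both powers in Step 3. It also narrows the gap, because the cut adds noise within communities and not between them. Suppose haemoglobin has an intracluster correlation of 0.012, the value that would explain the 1.7 above. The design effect is then 1 + 59 × 0.012 = 1.71 on the continuous scale. At 30% anaemia the yes/no correlation is about 0.576 × 0.012 = 0.0069, with design effect 1 + 59 × 0.0069 = 1.41. Information kept is 0.576 × 1.71/1.41 = 0.70, so the loss is about 30% rather than 42%. With fewer usable values per community it moves back towards 42%.

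**The case against.** Several points on the other side stand.

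- **The sentence is ambiguous.** The grammatical subject of the comparison in the Data Collection section is the haemoglobin data. A reader might infer that haemoglobin is compared only as anaemia and that comparing levels is ruled out. The article does not go that far: it names no comparison of levels, but does not exclude one.
- **This is a condensed article.** A full protocol or analysis plan, not shown, may already compare haemoglobin directly. The point therefore rests on the form the article does state, not on missing model detail.
- **Anaemia is a legitimate outcome.** It is a recognised clinical state, and a percentage anaemic is readily understood by the communities and policymakers the project serves. The loss in the table concerns detecting a shift in level, which is a different question from how many people are anaemic. The documents give no ground for replacing anaemia or demoting it.
- **Recovery is not ignored.** Prevalence is planned at baseline and follow-up and falls when someone recovers past the cut-off. The exclusion of people anaemic at baseline applies to incidence alone.
- **The number of usable values is unknown.** The 240 per group is the diet-quality sample. Haemoglobin comes from routine clinic tests, and section 3.3 (Ethics) lets participants consent to some parts and not others. Paired values may be well below 240 per group, possibly below 100.
- **A continuous analysis has its own difficulty.** A single mean across pregnant women, other women and young children is hard to interpret, and stratifying reduces precision within each stratum.

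What remains is that the stated form gives up information, and that a supplementary analysis would recover it from data already collected.

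**Conclusion.** The point holds as a modest, cheap improvement to a secondary outcome, not as an error or a contradiction. As written, haemoglobin is used to derive anaemia incidence and prevalence, and no comparison of level is named. For detecting a shift in level, the yes/no form loses about 36% to 78% of the information as anaemia prevalence runs from 50% down to 5%. This assumes normality, a uniform shift and independent observations; community clustering would make the loss somewhat smaller.

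A reader might want one headline figure such as 40–65%. The documents do not support it, because it needs an anaemia prevalence of about 10–35% and the article gives none. The power figures are illustrations, not estimates for this trial, since the shift, the prevalence and the number of usable values are all unknown.

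**What to change.** Keep anaemia prevalence and incidence as the reported outcomes, and add one analysis: a between-group comparison of follow-up haemoglobin as a continuous value.

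- Adjust for the person's baseline haemoglobin where a paired value exists.
- Allow for community.
- Include people who were anaemic at baseline.
- Stratify by women and children and by pregnancy, or express each value as its distance from the group-specific cut-off. The anaemia classification needs those cut-offs in any case.
- Report how many participants in each group have baseline, follow-up and paired values.

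If the full analysis plan already contains such a comparison, one sentence saying so settles the point.

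The cost is one extra analysis on data already to be extracted, with no new blood tests, visits or participants. A result in g/L is less familiar to communities than a percentage anaemic, so the two should be shown together. The gain is limited by however many participants have usable clinic values.

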##### Data Analysis

The difference in Dietary Guideline Index scores and food security status between strategy and control communities will be reported. Dietary intake and quality, food security status, anaemia incidence and prevalence, and discount card use will also be described. Diet cost and affordability data will be analysed using existing purpose-built data spreadsheets [36].

##### Qualitative Interviews

The design included the conduct of qualitative interviews with a sub-sample of 10–15 individual participants in each strategy community at baseline. The interviews were planned to be informed by an interview guide based on the literature including a study with urban Aboriginal and Torres Strait Islander people [47], exploring community members’ experiences of food insecurity. Data was planned to be managed in NVivo and thematically analysed, including by Aboriginal and Torres Strait Islander team members, and the findings interpreted by the wider research group as described above.

#### 3.5.2. Phase 2—Translation Phase

##### Design

The translational phase was designed to be informed by the outcomes of phase 1. We planned to use a qualitative methodology to develop a community-led framework and translation plan, with the goal of translating the research findings into sustainable changes in policy and practice (CREATE Tool item 11). This participatory design privileges the voices of community members, and therefore is inherently strengths-based (CREATE Tool item 10). Here, we outline early and broad plans, but it is intended that the process leading to the development of these outcomes will be informed by Community Advisory Groups, and therefore be community led.

First, photo voice methodology was planned to be employed to give a voice to remote community members’ lived experience of, and proposed solutions to, improving food security. Second, results from Phase 1 and the photo voice study, as well as evidence from recent food security events and inquiries, was planned to be presented to leaders within each participating community at community prioritisation workshops, with the aim to reach agreement on community-supported priorities and/or solutions to improve food security. Third, the community prioritisation results were planned to be considered at a knowledge exchange workshop facilitating the development of the community-led framework and translation plan (CREATE Tool item 11). To increase the translation of evidence into policy, concurrent to the aforementioned activities, we planned to test messaging using different frames to determine which is the most effective frame to address the key issues and solutions. This will ensure public receptiveness of the policy message and maximise traction of advocacy efforts to primarily non-Indigenous policymakers (CREATE Tool item 11).

##### Participants

It was planned that the participants in Phase 1 strategy communities be recruited for photo voice methodology. Community Advisory Groups can advise on who within each community should attend the community prioritisation workshops (CREATE Tool item 5). The knowledge exchange was planned to include up to 40 stakeholders, led by Community Advisory Groups with two representatives from each community (CREATE Tool item 8), as well as researchers, and policymakers. The design of the frame testing, to be conducted in the Gold Coast, Queensland, and Melbourne, Victoria, includes recruitment of members of the public aged over 18 years who speak English: at least 40 in intercept interviews and 20 in focus groups. A Qualtrics online panel was planned to be used to recruit 2000 Australian citizens in urban and regional locations who speak English and are aged over 18 years for the experimental framing study, with stratified sampling by age, gender, rural/urban location, school level, and voting preference to ensure the sample is representative of the wider Australian population.

### 3.6. Data Collection and Analysis

#### Photo Voice

Informed by Witnesses to Hunger [48], the co-design team aims to give greater voice to remote community members’ lived experience of food insecurity. The process was designed to be conducted in strategy communities, determined in conjunction with each Community Advisory Group and participants (CREATE Tool item 8). It was planned that participants have the opportunity to learn basic photography skills and about legal issues relating to privacy and copyright, representing capacity building for the community members participating (CREATE Tool item 13). It was planned that the key learnings from Phase 1 be shared, and the participants then take photos over an agreed timeframe to share their experience of and solutions to food insecurity. Information on theme generation is then shared, followed by participants collectively discussing the photos and arranging them into themes. The photos of most significance to participants are then discussed [49]. The researchers and participants will work together to determine how the data will be shared for the community prioritisation workshop in their community, and the knowledge exchange. In this way, participants have control over the data collection and interpretation (CREATE Tool item 8) and are assisted in presenting their stories of food security and insecurity and put forward policy solutions they feel are needed. This strengths-based approach inherently moves beyond practices of non-Indigenous researchers ‘reporting on problems in’ Aboriginal populations (CREATE Tool item 10).

### 3.7. Community Prioritisation Workshops

The community prioritisation workshops were designed to be informed by consensus building and deliberative democratic approaches [50,51,52]. The aim of the workshops is to achieve consideration of evidence and collective decision-making by community leaders, and agreement about community-supported priorities to improve food security to be shared at the knowledge exchange. The meeting procedure was planned to be negotiated with Community Advisory Groups (CREATE Tool item 5) and include the presentation of evidence, facilitated discussion, and finally prioritisation of the priorities and/or solutions to improve food security using the Ripple Tool [53]. The expected outcome is that representatives from each community will provide a summary of the discussion and final prioritisation outcomes for their community at the knowledge exchange.

### 3.8. Knowledge Exchange

Finally, we planned to bring together representatives from all strategy and control communities to conduct a knowledge exchange to develop a community-led framework to improve household food security in remote communities (CREATE Tool item 11). This was planned to include mapping of evidence from Phase 1, and the preceding parts of Phase 2 against existing food security determinant frameworks [54]. A translation plan will be developed, informed by a frame analysis.

### 3.9. Frame Analysis

We planned to develop and test with the public a range of frames, informed by the photo voice methodology and the community prioritisation outcomes. We planned to conduct intercept surveys in public spaces which collect age, gender, level of education, voting intention, and quantitative level of agreement and qualitative responses to different policy actions designed to improve food security among Aboriginal and Torres Strait Islander peoples. Descriptive analysis was planned to be conducted with demographic and level of agreement data, and a framing analysis will be undertaken with the qualitative data. Several pilot messages using the key frames from the intercept surveys will be developed. Through focus groups, we planned to then explore how understandable these pilot messages are and if they provoke thoughts or feelings towards the policy actions. Qualitative data will be managed in NVivo and thematically analysed. The messages will be further refined based on the focus group feedback. We then expect to conduct an experimental framing study using the three most effective messages from the focus groups plus a control. This study will determine which message framing will have greatest likelihood of increasing the acceptability of the proposed policy solution. Participants are planned to be stratified into four nationally representative groups which will receive the same policy solution framed in different ways. A short survey on level of support for the policy was planned, asking participants how they feel about the policy, and whether they think the policy will be effective.

## 4. Discussion

Through the co-design process employed in its design, the Remote Food Security Project takes a strengths-based approach that fits within a human rights, social justice, and empowerment agenda, therefore responding to calls from ACCHOs to support food security in remote Aboriginal and Torres Strait Islander communities in Australia. The result of having the co-design process underpinned by the Research for Impact Tool is a project that delivers on a solution proposed in Apunipima’s call to action and aligned with Congress’ research priorities, uses participatory methods, and has a strong translation focus. A challenge found in applying this best practice tool was in negotiating details with community members within tight grant timelines, and in being mindful of taking time and setting expectations in the community without guaranteed funding. However, in defining the evidence needs of the users, it was clear that we were responding to Apunipima’s call to action. We also ensured that the design which was participatory in nature allowed for community direction; and this has been shown, for example, by who governs and directs the project locally.

As identified, there was significant overlap between these two complementary tools, which was further highlighted when the CREATE Tool was applied to our co-design process in line with the Research for Impact Tool steps. We found the Research for Impact Tool useful in considering our broad approach that focused the design development on the users’ needs (steps 1–3) and in aiming to deliver genuine benefit to communities (steps 4–6). The CREATE Tool, which similarly focuses on these issues, allowed us to check on the steps we were planning in the research process. All tool items have been addressed in the design of the Remote Food Security Project. However, whilst our agreements with ACCHOs are legally binding, our agreements with Community Advisory Groups are in line with processes conducted in the regions and are governed by our ethics applications and are not legally binding (CREATE Tool item 6). We believe these two tools, especially when used together, support co-design processes that genuinely partner with Aboriginal and Torres Strait Islander communities and researchers for community benefit. Since our application of these tools, although not informed by a research lens, a review of optimal approaches to co-design in health care policy, practice, and service provision with Aboriginal and Torres Strait Islander people has been published [55]. The six themes of co-design identified in the review are reflected in the steps and questions of the tools we applied which are specific to the research setting. The review offers further detailed and practical sub-themes which would assist in operationalising these broad themes. Partnerships between peak health organisations and academics, especially when guided by best practice tools such as the Research for Impact Tool and the CREATE Tool, can strengthen research to deliver community benefit. This approach, undertaken in remote Australia, has application to other contexts nationally in considering the creation of evidence with groups impacted themselves, to inform policy decisions in line with the UN Declaration of the Rights of Indigenous Peoples.

The Remote Food Security Project directly responds to a call to action from Apunipima to test a direct-to-consumer food subsidy scheme to address financial barriers and increase affordability and access to healthy food and drink in remote areas. The price discount directly addresses the high cost of food in remote communities. Following testing of the price discount, the project will work with Community Advisory Groups and participants to collect local evidence that is expected to address other determinants of food security in Cape York and Central Australia. Together these forms of evidence will provide community members and the ACCHOs servicing them with a collective understanding of the many factors influencing food insecurity, and a picture of the solutions for policymakers, in community members’ own words. Our message testing with the public will help ensure these policy messages are informed by what is considered broadly acceptable, and therefore have the best opportunity to gain traction in policy settings.

